## ***Phase II: Evaluating a complex intervention***

**Design:** In this phase an assessor-blind, parallel randomised controlled trial (RCT) will be conducted to evaluate the effects of the MCI on sexual adjustment as the primary outcome among premenopausal women treated for BRC, relationship quality and QoL as secondary outcomes among the women and their partners. There are three research hypotheses: participants in the intervention will have better 1) sexual adjustment, 2) relationship quality, and 3) QoL, after the completion of the intervention than those in the attention control group.

**Sample size:** The sample size is determined to give the study adequate power to evaluate the effects of the MCI on the outcomes of sexual adjustment, relationship quality and QoL. To our knowledge, no study has investigated the effects of a multimodal couple-based intervention on sexual health outcomes. Without an empirically-derived effect size to guide our sample size planning, we instead define a clinically relevant change as a 0.5 standard deviation (SD) improvement in the above outcomes on *a priori* basis. Such an effect corresponds to a medium effect size [33] and is empirically regarded as a minimally important difference [34]. By using the power analysis software PASS 16 (NCSS, LLC, Kaysville, Utah, USA), it is estimated that a sample size of 64 dyads per group is adequate to achieve 80% power at two-sided 5% level of significance to detect an effect size of 0.5 SD in an outcome at a post-intervention time point. Further allowing for an overall attrition rate up to 20% [21], a total of 160 eligible dyads with 80 per group will be recruited into the RCT.

**Settings and subjects:** The inclusion criteria for women treated for BRC and the recruitment process described in Phase II will apply to this phase, but subjects will be women completed active treatment for BRC in recent six months but endocrine and/ or maintenance therapy allowed, and with no evidence of metastatic disease, so that the intervention will be delivered to them during early survivorship, with the intent to prepare the women and their partners for life after cancer. Partners of the eligible subjects will be recruited as in dyad. HK\$150 cash coupon will be given to each participant for time compensation on completion of all reassessments.

**Procedure:** Eligible women and their partners will be approached in the oncology clinic and have the aims of the study explained to them. Information sheets about the study and consent forms will be

provided. After written consent is obtained, the participating dyad's demographic data will be collected and the instruments administered during baseline face-to-face interviews. The participants will then be randomly assigned to either the intervention or attention control group. Subject allocation will be done using stratified block randomisation with a block size of 10. A random sequence of grouping identifiers (I or C), based on computer-generated random numbers, will be prepared in advance by an independent statistician. The grouping sequence lists will be password-protected and stored in a computer, and only be accessible to staff independent of the study or responsible for group allocation. The group allocation of each participant will be assigned according to the sequence of enrolment and the corresponding group identifier in the previously prepared random sequence list. The trained research nurse will deliver the MCI to the participants and their partners. In order to ensure the fidelity of the intervention, the PI will monitor the intervention delivered to the first 10 dyads. Reflective notes and a record of the participants' attendance will be kept as a means of process evaluation. To ensure blinding of the outcome assessor, a part-time research assistant who will not be informed of the group status of the participants will be responsible for reassessment. Reassessment will be conducted at the same time point for both groups, i.e. on the completion of the intervention, three months and six months post-intervention via telephone call. Participating dyads in the intervention group will be invited to be interviewed about their experiences and feelings towards the intervention, and will be audio-taped. Another research nurse will conduct qualitative interviews with the participating dyads to prevent an experimenter effect.

**Data collection:** Participation and completion rates of the intervention by the participating dyads in the intervention group will be monitored. A demographic and clinical data sheet will be used to record the socio-demographic and clinical characteristics of the participants. Effects of the intervention on the outcome variables will be measured at baseline (T0), on completion of the intervention (T1), three months (T2) and six months (T3) post-intervention by using the following measures:

1. *Chinese version of the sexual adjustment scale of the Sexual Adjustment and Body Image Scale (SABIS)*

The Chinese version of the sexual adjustment scale of SABIS will assess the effect of the MCI on sexual adjustment among the women treated for BRC. The SABIS consists of two scales: a six-item body image scale and an eight-item sexual adjustment scale. Using a five-point Likert scale with scores ranging from 1 to 5, higher scores indicate better outcomes. The scale has been used previously in BRC with good reliability and validity [9]. While no Chinese version is available, we have developed one using the Brislin model of translation and guidelines for cross-cultural adaptation of scales. The translated version of SABIS will be assessed for semantic equivalence and content validity by a panel of six healthcare professionals, with a content validity index of 0.8 or above set as the satisfactory criteria, and revised if necessary, before administration to participants.

2. *Chinese version of ENRICH Marital Satisfaction Scale (EMS)*

The Chinese version of EMS will be used to assess the quality of partner relationships of the participating dyads individually. It consists of 10 items, extracted from the original full-length 125-item ENRICH Marital Inventory, which are recognised as the most important dimensions of relationships by the original author. A five-point Likert scale with scores ranging from 1 to 5 is used, with higher scores indicating better relationships. The scale has established discriminant validity and demonstrated good reliability, with an internal consistency of 0.76 [35].

3. *Chinese version of the MOS 36-item Short Form (SF-36) Health Survey*

QoL of the participating dyads will be measured by the Hong Kong Chinese version of the SF-36. The 36 items are clustered into eight domains: physical functioning (PF), role physical (RP), bodily pain (BP), general health (GH), vitality (VT), social functioning (SF), role emotional (RE), and mental health (MH). All items in each domain are summed and transformed into scales from 0 to 100. Furthermore, the PF, RP, BP, and GH domains are aggregated into the physical health component summary (PCS) score, and the VT, SF, RE, and MH domains are aggregated into the mental health component summary (MCS)

score. Higher scores indicate better QoL. The Hong Kong Chinese version of the SF-36 has demonstrated good construct validity, internal consistency and test-retest reliability among Chinese patients in primary care [36].

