The proposed MCI will be an eight-week five-session programme, each session delivered every two weeks (at Weeks 0, 2, 4, 6, and 8), and covering topics on the impact of BRC on sex and intimacy, communication and problem-solving skills, dyadic positive coping, cognitive restructuring of sex and intimacy, intimacy-building activities, and maintaining intimacy [18,21,23-25]. The first and last sessions will be conducted in face-to-face dyad format, the second session will be virtual dyad counselling, the third one will be online reading with chat-based discussion forum and homework exercise, and the fourth will be reminder telephone call for reviewing what has been achieved and scheduling the last session. The counselling sessions will last for 60-90 minutes and delivered by a full-time research nurse who will receive one-week training from the PI to provide the intervention, while the online discussion will be moderated by the research nurse to monitor the progress of sensate focus practice which is a common technique used in sex therapy to improve intimacy and communication between partners around sex. The telephone call will last for around 30 minutes. Components and contents of the MCI are listed in Appendices A and B.

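### One fixed block size of 10, disclosed in the protocol, leaves a limited and avoidable risk to allocation concealment because nothing states that recruiting staff are unaware of past allocations

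*Protocol*

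**What the plan says.** All of this is in the protocol. Unless another section is named, it comes from the Phase II part.

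- **Method.** Allocation uses "stratified block randomisation with a block size of 10". The stratification factors are not named.
- **Ratio.** "a total of 160 eligible dyads with 80 per group will be recruited into the RCT", which is 1:1.
- **Sequence.** It "will be prepared in advance by an independent statistician". Each dyad's group is "assigned according to the sequence of enrolment and the corresponding group identifier in the previously prepared random sequence list".
- **Access.** The lists are password-protected and "only be accessible to staff independent of the study or responsible for group allocation".
- **Timing.** Written consent and the baseline instruments come first. Then: "The participants will then be randomly assigned to either the intervention or attention control group".
- **Delivery.** "The trained research nurse will deliver the MCI to the participants and their partners". The section on developing the intervention describes the counselling sessions as "delivered by a full-time research nurse who will receive one-week training from the PI to provide the intervention", which points to one person.
- **Blinding.** The part-time research assistant who does the reassessments is the only person said to be uninformed of group.
- **Records.** The section on data handling and record keeping opens study data and records to the investigators and all employed research staff, both during and after the study. It makes no exception for group status.

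The protocol does not say who approaches and enrols Phase II couples, or who delivers the attention control.

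**The concern.** A permuted block of known size gives information away as it fills. Once five dyads of one arm have appeared in a block of 10, every remaining place belongs to the other arm. Password protection stops someone reading the list. It does not stop someone deducing the next entry from past assignments and the block size, and the block size is printed in the protocol.

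Approaching the couple, obtaining consent and taking the baseline interview all come before assignment, so these are the steps that a forecast of the next arm could influence. The primary outcome is a self-reported Likert score for sexual adjustment, and the intervention needs both partners to engage. If more motivated couples were steered or timed towards one arm, the comparison would be biased. Adjustment for measured baseline scores would remove only part of that bias.

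**Working it through.** **Inputs.** Block size 10 and 160 dyads at 80 per group, both from the Phase II section. The total follows from the protocol's own figures: 64 / (1 − 0.20) = 80 per group, and 2 × 80 = 160. With 1:1 allocation, each block has n = 5 per arm, and 160 / 10 = 16 blocks if all fill. The protocol gives no figure for predictability, so there is none to reproduce.

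**Assumed observer.** This person knows the block size, the order of enrolment within the stratum and every earlier assignment in it, controls included.

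**Assignments known with certainty.** A given place in one arm is certain if it falls after all n places of the other arm, which has probability 1/(n + 1). There are 2n places, so the expected number per block is

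2n / (n + 1) = 10 / 6 = 1.67 of 10, or 16.7%.

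Over 16 full blocks: 16 × 1.67 = 26.7, about 27 of 160.

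**Where in the block they fall.** Place k is certain if one arm is used up in the first k − 1 places, with probability 2 × C(k − 1, 5) / C(10, 5), where C(10, 5) = 252.

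| Place | Calculation | Probability certain |
|---|---|---|
| 1–5 | – | 0 |
| 6 | 2 × 1 / 252 | 0.008 |
| 7 | 2 × 6 / 252 | 0.048 |
| 8 | 2 × 21 / 252 | 0.167 |
| 9 | 2 × 56 / 252 | 0.444 |
| 10 | 2 × 126 / 252 | 1.000 |

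These add to 1.67, which agrees with the formula. Most of the certainty lies in the last two places, so blocks left unfilled contribute little. As an illustration, assume four strata that each end with a half-filled block. Then 20 dyads are in those blocks and contribute nothing, and the other 140 fill 14 blocks: 14 × 1.67 = 23.3.

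**Best-guess accuracy.** Always guessing the arm with fewer assignments so far in the block is right, per block, on average

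n + ½ × (4ⁿ / C(2n, n) − 1) = 5 + ½ × (1024 / 252 − 1) = 6.53 of 10, or 65.3%,

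against 50% by chance.

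**Comparison of schemes.** Fixed sizes are exact. Varying sizes are simulated on a single unstratified list of 160, for a guesser who knows the set of sizes but not their order.

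| Scheme | Known with certainty | Best guess correct |
|---|---|---|
| Fixed 4 | 33.3% | 70.8% |
| Fixed 6 | 25.0% | 68.3% |
| Fixed 10 (protocol) | 16.7% | 65.3% |
| Random 4, 6, 8 | 2.3% | 68.0% |
| Random 6, 8, 10 | 1.5% | 66.3% |

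Varying the size nearly removes certain prediction. It does nothing for best-guess accuracy.

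**The case against.** The strongest reply is that the protocol already protects allocation: an independent statistician prepares the sequence, the list is password-protected with restricted access, and assignment follows consent and baseline. That is correct, and releasing assignments only after consent and baseline needs no change. Ten is also a comparatively safe fixed size, less predictable than 4 or 6.

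A second reply is that bias needs a chain the protocol does not describe. A reader might infer that staff and dyads see each allocation as it happens, or that the nurse who delivers the intervention also recruits. The text says neither. A dyad learns at most its own arm, after enrolment, which predicts nothing for anyone else. The nurse is shown to know the intervention dyads only. Without the control assignments and the enrolment order within strata, the nurse cannot tell where a block stands. Recruitment is described without naming who does it, and such duties may be set out in a document that is not at hand.

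A third reply is that baseline is measured before allocation and enters the GEE comparison of change, so imbalance in measured scores would be visible and partly handled. This stands too, although unmeasured differences such as motivation would remain.

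Together these replies narrow the point but do not remove it. The block size is fixed and disclosed in the protocol itself. List access extends to staff responsible for allocation, who need not be independent. Nothing in the protocol shields past allocations from those who recruit.

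**Conclusion.** The point holds as a limited, conditional risk to concealment, and the remedy is a cheap improvement. Up to about 1 in 6 assignments, at most about 27 of 160, could be known with certainty. This is a ceiling: it assumes that all 16 blocks fill and that one observer follows every assignment in every stratum. Selection bias would further require that this observer recruits couples or informs someone who does, which the protocol neither states nor excludes.

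A reader might conclude that upcoming assignments are predictable in general, or that concealment has failed. The document does not support either. Certainty is confined to the second half of a block, and the protocol describes no breach. The sample size and the planned analysis are unaffected.

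**What to change.** 1. Have the independent statistician generate the lists with randomly varying block sizes (for example 6, 8 and 10). Replace the stated block size in the protocol with a sentence saying that sizes vary and are recorded in a restricted document.
2. State that the list is held by a person who neither approaches couples nor delivers the intervention, and that recruiting staff have no access to the list or to the running record of past allocations. Add a matching exception to the access rule in the section on data handling and record keeping.

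Both parts are needed. The first cuts certain prediction from about 17% to about 2%, but best-guess accuracy stays at about 65–66%, and only the separation of roles deals with that.

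The cost is a small change to the list-generating program and a few sentences of protocol text, best made before the first dyad is randomised. The loss of balance is negligible: with no block larger than 10, the arms within a stratum can never differ by more than 10 / 2 = 5 dyads, the same bound as now. No extra dyads are needed.

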#### 4. Demographic and clinical data sheet

A data collection sheet will record the socio-demographic and clinical characteristics of the BRC women: age, education level, monthly household income, marital status, duration of marriage/current relationships, number of children, religious beliefs, stage of cancer, time since diagnosis, treatment modality and length of treatment. Socio-demographic data of the partners will also be collected: age, education level, medical and drug history.

Qualitative data will be collected from the intervention group through semi-structured interviews up to the point of data saturation, estimated to be 20 participating dyads. Their experiences and perceptions of the MCI, and whether the programme improved their sexual adjustment will be explored. The interviews will be scheduled after the completion of the programme, and audiotaped with consent.

**Data analysis:** Data will be summarised and presented using appropriate descriptive statistics. The homogeneity of participants' characteristics between the two study arms will be assessed using independent t, Mann-Whitney, chi-square or Fisher's exact tests, as appropriate. Intention-to-treat principle will be adopted in the outcome analysis by using a generalised estimating equations (GEE) model to compare the differential changes in each outcome across the four time points between the two arms. All statistical analyses will be performed using SAS release 9.4 (SAS Institute, Cary, NC.). All statistical tests are two-sided with level of significance set at 0.05. Audiotapes of the interviews will be examined by means of content analysis. First, the recorded tapes will be transcribed verbatim. All transcripts will be compared with the recording to check for any discrepancies, and revised as necessary. The transcripts will then be content analysed to identify persistent words and code themes within the data. Finally, significant categories and themes of the data will be formulated and confirmed by the PI and Co-I to improve its accuracy, and then translated into English [37].

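### The sample size is worked out for a between-arm difference at one follow-up visit, but the planned GEE reads as a test of difference in change from baseline: the 80% power is not guaranteed for that test, and adjusting for T0 would be more precise

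*Protocol*

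**What the plan says.** Protocol, section iii, Phase II, Sample size: the effect is introduced with "we instead define a clinically relevant change as a 0.5 standard deviation (SD) improvement in the above outcomes". The power statement then says that "a sample size of 64 dyads per group" is "adequate to achieve 80% power at two-sided 5% level of significance" and is meant "to detect an effect size of 0.5 SD in an outcome at a post-intervention time point". Allowing for up to 20% attrition brings recruitment to 80 per group, 160 dyads in all. The paragraph gives no correlation between baseline and follow-up, no SD of change and no repeated-measures term.

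Phase II, Data analysis: each outcome goes into a GEE model whose purpose is to "compare the differential changes in each outcome across the four time points between the two arms". On error rates: "All statistical tests are two-sided with level of significance set at 0.05". The Data collection paragraph lists the time points as T0 (baseline), T1, T2 and T3, so baseline is one of the four. The paragraph does not mention T0 as a covariate or a common baseline mean for the two arms.

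**The concern.** The two paragraphs describe different quantities. The sample size rests on the spread of the score at one visit. A difference in change rests on the spread of the change, which depends on how strongly follow-up scores track baseline. Unless that correlation is exactly 0.5, the two comparisons have different power for the same true difference.

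Two things are at stake. First, the power quoted for the primary outcome (sexual adjustment in the women) may not belong to the test that will be run. Second, T0 is collected from every participant before randomisation. Subtracting it, as a change contrast in effect does, uses that information less efficiently than adjusting for it.

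**Working it through.** **Inputs from the protocol.** Two-sided alpha 0.05; power 80%; effect 0.5 SD; 64 evaluable per group; attrition 20%; 1:1 allocation; measurements at T0, T1, T2 and T3.

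**Assumptions.** rho, the correlation between baseline and a follow-up visit, is not in the protocol and is taken over 0.3 to 0.7. The score SD is the same at each visit, and 0.5 SD means 0.5 of the score SD.

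**Step 1: reproduce the plan's figure.** For a two-sample t-test at one visit, the non-centrality is 0.5 × sqrt(64/2) = 2.83 with 126 degrees of freedom. This gives power 0.801; 63 per group gives 0.795, so 64 is the smallest adequate size. Then 64/0.8 = 80 per group and 160 in total. The stated arithmetic is correct, and it contains no correlation.

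**Step 2: difference in change, with arm-specific baseline means left free.** The SD of a change is SD × sqrt(2(1 − rho)), so the standardised effect is 0.5/sqrt(2(1 − rho)). At rho 0.3 this is 0.5/1.183 = 0.423.

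**Step 3: difference adjusted for T0.** The residual SD is SD × sqrt(1 − rho²), so the standardised effect is 0.5/sqrt(1 − rho²). At rho 0.3 this is 0.5/0.954 = 0.524.

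**Step 4: results for one follow-up visit (non-central t).**

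| rho | Change: power, 64 per arm | Change: evaluable n per arm for 80% | T0-adjusted: power, 64 per arm | T0-adjusted: evaluable n per arm for 80% | Variance ratio, change / adjusted |
|---|---|---|---|---|---|
| 0.3 | 66.0% | 89 | 83.7% | 59 | 1.54 |
| 0.4 | 72.7% | 77 | 86.5% | 54 | 1.43 |
| 0.5 | 80.1% | 64 | 90.0% | 49 | 1.33 |
| 0.6 | 88.1% | 52 | 93.9% | 42 | 1.25 |
| 0.7 | 95.2% | 39 | 97.6% | 34 | 1.18 |

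The last column is 2(1 − rho)/(1 − rho²) = 2/(1 + rho), which exceeds 1 for every rho below 1. The change contrast matches the stated 80% only at rho 0.5. It falls short below that value and does better above it.

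**Step 5: would a joint test over the three follow-up visits alter this?** Take a constant 0.5 SD effect, exchangeable correlation and 64 per arm. The 3-degree-of-freedom arm-by-time test then has power of about 69% at rho 0.3, 84% at 0.5 and 98% at 0.7. The dependence on rho remains.

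**The case against.** The strongest reply has four parts.

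- **No shortfall is shown.** This stands. A reader might infer from the mismatch that the trial is underpowered. The protocol does not support that: it gives no rho, and at 0.5 or above the change contrast has at least the stated power. Some design features give reason for caution: baseline is taken face to face and follow-up by telephone, women enter soon after active treatment, and the primary scale is a new translation. None of these shows that rho is below 0.5.
- **The SD is ambiguous.** This stands in part. The sample-size paragraph speaks of a change and an improvement. If 0.5 were in units of the SD of change, 64 per group would apply directly to a change comparison. The power sentence itself, which refers to an outcome at a visit, favours the score SD. Under the other reading the detectable score difference would itself vary with rho, from 0.5 × 1.183 = 0.59 score SD at rho 0.3 to 0.5 × 0.775 = 0.39 at rho 0.7. The protocol should say which is meant.
- **The parameterisation is inferred and may be settled in a statistical analysis plan.** This stands in part. Model terms can be left to that plan, and a GEE with a common baseline mean is compatible with the protocol's wording. But the protocol is not merely silent. It states one quantity for power and another for analysis, and both statements are its own.
- **The calculation is for a single visit with 64 per arm.** True. 64 is the floor after attrition, and earlier visits may have more participants. The powers above belong to that contrast and are not the power of every test the GEE could supply.

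The unconstrained contrast is also valid and unbiased in a randomised trial. The point concerns precision and the basis of the power statement, not bias.

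**Conclusion.** The point holds in conditional form. The protocol powers a difference at one visit and, on the most natural reading, analyses a difference in change. With arm-specific baseline means left free and 0.5 taken as score SD, single-visit power with 64 per arm runs from 66% to 95% over rho 0.3 to 0.7. The 80% is therefore not guaranteed for the planned contrast, but it is not shown to be wrong, and the sample-size arithmetic is sound.

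The loss of precision against baseline adjustment does not depend on where rho lies: with equal variances over time it applies at every rho below 1, with a variance 18% to 54% larger over rho 0.7 to 0.3. It does depend on the unconstrained form being the one used. The change is worth making before analysis; the design does not fail without it.

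**What to change.** **Data analysis paragraph.** Model T1, T2 and T3 as the responses, with arm, time, arm × time and the participant's own T0 score as a covariate. Report the adjusted between-arm difference at each visit.

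An acceptable alternative keeps T0 among the responses, with a common baseline mean for the two arms and a working correlation other than independence (exchangeable or unstructured, for example). The constraint is legitimate because baseline is measured before randomisation. The working correlation matters: under independence with complete data, the visits are fitted separately, and the constrained model returns the raw follow-up difference with no gain from T0.

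**Sample-size paragraph.** State that 0.5 SD refers to the SD of the score and that 80% is the power of the unadjusted comparison at one visit. The T0-adjusted analysis essentially meets or exceeds this for any non-negative rho.

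**Cost.** A few sentences in two paragraphs. The 160 dyads, the visits, the GEE approach and the software stay as they are.
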